**Methods and analysis:**

At least 200 children aged 6–16 years at-risk of FASD will be recruited across at least seven study sites. Following standards for reporting diagnostic accuracy study (STARD) guidelines, all children will complete index and reference tests. Diagnostic accuracy statistics (including receiver operating curves, sensitivity, specificity, positive and negative predictive values and likelihood ratios) will identify whether rapid assessments can accurately identify: (1) the presence of an FASD diagnosis and (2) impairment in each neurodevelopmental domain, compared to comprehensive assessments. Direct and indirect healthcare costs for index tests compared to reference tests will be collected in primary healthcare and specialist settings.

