#### Participants

Two hundred families enrolled in Phase I will be asked about caregiver costs associated with index tests and reference tests. All sites will record health service costs associated with index tests and reference tests. Sites conducting comprehensive reference FASD assessments prior to the study will record health service costs of usual care for FASD assessments retrospectively.

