#### Procedure

Prior to participant recruitment, the cost of index and reference tests (usual care) for health services will be retrospectively collected in a structured phone/video interview from site managers. Site manager responses will be recorded, transcribed and data will be extracted. Expected completion time for index and reference tests will also be extracted from test manuals. Families will be recruited and enrolled in the study as outlined in Phase I. Enrolled families and healthcare practitioners will complete surveys with one member from the research team that capture prospective cost information at the completion of testing. Therefore, the cost of index and reference tests will be collected retrospectively for tests administered as part of prior usual care from health service interviews, and costs will be collected prospectively for patients and health services recruited during the study period.

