#### Phase II: economic analysis

A multivariable generalised linear model of the cost of diagnosis, with the predictive variable as the index test or reference test, will estimate the incremental cost between the two alternative diagnostic processes adjusting for differences in patient geographical location and other potential confounders. Subgroup cost analysis will explore heterogeneity of results between patients’ subgroups by including an interaction term (e.g., location, diagnostic procedure) within the multivariable generalised linear model of cost. The expected value of implementation will be calculated as the net monetary benefit of the index tests (i.e., monetary benefits — costs) multiplied by the population of patients expected to benefit from the reference tests. Probabilistic and one-way sensitivity analysis will be used to characterise the uncertainty in the economic results, highlighting the most important drivers for the value of implementing the index tests.

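### The Phase II cost model does not use the within-child pairing of index and reference costs; fitted as stated, its interval for the incremental cost would probably be too wide, by an amount the article does not let us fix

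*Protocol article*

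**What the plan says.** The cost comparison is within child by design. The Abstract (Methods and analysis) says that "all children will complete index and reference tests". Phase II, Participants, says: "Two hundred families enrolled in Phase I will be asked about caregiver costs associated with index tests and reference tests". Phase II, Procedure, adds that enrolled families and practitioners give prospective cost information once testing is complete.

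The Data analysis section for Phase II then specifies "A multivariable generalised linear model of the cost of diagnosis, with the predictive variable as the index test or reference test", which "will estimate the incremental cost between the two alternative diagnostic processes adjusting for differences in patient geographical location and other potential confounders". Subgroup heterogeneity is to be explored by "including an interaction term (e.g., location, diagnostic procedure) within the multivariable generalised linear model of cost". The section mentions no paired difference, repeated measure, child-level effect or clustering. It names no distribution family or link.

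Not every cost is paired. Phase II, Participants, also says: "Sites conducting comprehensive reference FASD assessments prior to the study will record health service costs of usual care for FASD assessments retrospectively". Phase II, Procedure, confirms that "the cost of index and reference tests will be collected retrospectively for tests administered as part of prior usual care from health service interviews". The article does not say whether these retrospective figures enter the regression.

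**The concern.** The stated model reads as a comparison of two groups of patients, whereas the prospective data are two costs from each child. An ordinary generalised linear model takes its rows as independent. Two rows from one child are unlikely to be independent: remoteness, travel and accommodation, for instance, can raise both costs for the same family.

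The stated purpose of the adjustment fits the design poorly as well. A child's location is the same on the child's index row and reference row. In complete pairs there is therefore no difference in patient location between the two alternatives to adjust for. Location can change the size of the cost difference, but it cannot confound it.

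At stake is the stated precision of the incremental cost. That cost bears on the net monetary benefit in the same section, and its uncertainty is a natural input to the planned probabilistic sensitivity analysis. By contrast, the Phase I analysis uses the pairing openly, through correlations of matched scores and Bland-Altman plots.

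**Working it through.** **The plan's own figures.** The article gives no standard error, power or sample size for the cost model. Its only precision figures are for Phase I, and they reproduce: with 200 × 0.55 = 110 children with FASD and 90 without, 1.96 × √(0.8 × 0.2/110) = 7.5% and 1.96 × √(0.9 × 0.1/90) = 6.2%. They have no bearing on the cost analysis.

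**Inputs.** Pairing and the form of the model come from the article. The within-child correlation ρ and the ratio k of the reference-cost SD to the index-cost SD are not given, so both are assumed and varied.

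**Incremental cost (reference minus index, n complete pairs).** With the index SD set to 1:

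- SE with independent rows: √((1 + k²)/n)
- SE using the pairs: √((1 + k² − 2ρk)/n)
- Inflation: √[(1 + k²)/(1 + k² − 2ρk)]

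| k | ρ = 0 | ρ = 0.3 | ρ = 0.5 | ρ = 0.7 |
|---|---|---|---|---|
| 1 | 1.00 | 1.20 | 1.41 | 1.83 |
| 2 | 1.00 | 1.15 | 1.29 | 1.51 |
| 4 | 1.00 | 1.08 | 1.14 | 1.22 |
| 18 | 1.00 | 1.02 | 1.03 | 1.04 |

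For example, at k = 1 and ρ = 0.5 the inflation is √(2/1) = 1.41; at k = 18 and ρ = 0.5 it is √(325/307) = 1.03. The value 18 supposes that SDs scale with testing time. The article gives around 2 days for the reference assessment (taken here as 15 hours, or 900 minutes) and 30 + 20 = 50 minutes for the index tests, and 900/50 = 18.

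The error is conservative: a nominal 95% interval would cover about 99.4% at inflation 1.41 and about 97.5% at 1.14.

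**Check with a gamma, log-link model.** This was simulated with 200 children, 400 replicates, an assumed mean cost ratio of 4, log-SD 0.5 for both costs, ρ = 0.5, and location in the model. The average model SE of the log cost ratio was 0.0528. The actual sampling SD was 0.0378 and the child-clustered SE was 0.0385. The inflation is 0.0528/0.0378 = 1.40, close to the equal-SD row, as expected for a ratio with equal relative spread. A second simulation with a coefficient of variation of 0.6 gave 0.0598/0.0447 = 1.34.

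**Between-child effects.** For a covariate that is constant within child, the naive-to-true SE ratio is √[(1 + k²)/(1 + k² + 2ρk)]. At ρ = 0.5 this is √(2/3) = 0.82 for k = 1, √(17/21) = 0.90 for k = 4 and √(325/343) = 0.97 for k = 18. These SEs are too small. The planned test-by-location interaction compares within-child differences between locations, so it errs in the same direction as the main contrast.

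**Bias and the role of location.** With complete pairs, the simulated bias of the log cost ratio was at most 0.003, with or without location. In a scenario where 60% of remote children (30% overall) lacked a reference cost, the bias was −0.0905 unadjusted, or exp(−0.0905) − 1 ≈ −9%, and −0.0019 with location in the model. That missingness pattern is assumed, not taken from the article.

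**The case against.** A reader might infer that the plan treats the two costs as coming from different patients, so that its standard errors are simply wrong. The text does not say so. It names a model and a predictor and is silent on covariance. A generalised linear model can carry generalised estimating equations, child-clustered standard errors or a child-level bootstrap, and a condensed article may leave that choice to the full plan. This objection stands to the extent that the conclusion must be conditional. It does not remove the point, because the wording on adjustment describes between-patient differences that the paired design does not have.

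A reader might also infer that the adjustment addresses confounding that cannot exist. That holds only for patient-level covariates in complete pairs. Pairs may be incomplete, since the Sample size section allows for 30% attrition. The retrospective usual-care costs do not come from enrolled children. Practitioner discipline, mode of delivery and travel can differ between one child's two tests. The primary-care versus specialist comparison is not stated to be within child. Location therefore belongs in the model.

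Three further objections hold. The location interaction is already planned. The error in the main contrast is conservative. And if the incremental cost is read as an absolute difference, the much longer reference assessment may dominate the variance and make the inflation small. The article lists no location main effect among its outcomes, so the too-small standard errors matter only if such an effect, or another between-child contrast, is reported from this model. All economic outcomes are secondary.

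**Conclusion.** The point holds in a limited form. The prospective comparison is paired, and the stated model does not use the pairing. If it is fitted as stated and a child's two costs are positively correlated, the interval for the incremental cost is too wide: by a factor of about 1.03 to 1.41 at an assumed correlation of 0.5, depending on how unequal the two SDs are, and not at all if the correlation is zero. Standard errors for between-child effects would be too small, by up to about 18% at that correlation.

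The point estimate is unbiased with complete pairs. The document does not establish that the rows will be analysed as independent, and it does not support calling the location adjustment pointless. This is a loss of precision and a mismatch between design and wording in a secondary analysis. It is worth correcting because the correction is simple.

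**What to change.** In the Data analysis section for Phase II:

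- State that the child is the clustering unit, through generalised estimating equations with robust standard errors, a child random effect, or a bootstrap that resamples children together with both their costs.
- Report the mean within-child cost difference with its interval.
- Keep location as a covariate, with the interaction already planned, and say which covariates can differ between a child's two tests.
- Analyse the retrospective site-level usual-care costs separately from the child-level model.

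The cost is a few lines of wording and slightly more analysis work. No new data are needed.

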### Summary

This research aims to establish the accuracy and cost-efficiency of rapid, culturally-responsive screening and assessment tools, which are part of a co-designed, tiered neurodevelopmental assessment process for diagnosing FASD in primary healthcare.^17 22–24^ Diagnosing children with FASD in primary healthcare will lessen the burden on specialist systems and help to place developmentally and socially/emotionally vulnerable children on support trajectories earlier. Our findings will help to demonstrate how primary healthcare, which is readily available to families regardless of their location, can support the assessment of FASD. Even partially adding information available to specialists can streamline subsequent interventions. Providing primary healthcare practitioners with the knowledge and tools to quickly identify children who are developmentally at-risk, to understand when to diagnose children and when to seek specialist involvement, will reduce the demand on overburdened specialist clinics. This will assist in providing timely access for assessment and treatment of children suspected of having FASD in Australia.

## Ethics and dissemination

### Ethics

The study has received ethical approval from the Griffith University Human Research Ethics Committee (2020/743) and Children’s Health Queensland Hospital and Health Service Human Research Ethics Committee (HREC/20/QCHQ/63173). Consent to conduct research was obtained from the Kalkadoon Native Title Aboriginal Corporation Registered Native Title Bodies Corporate, representing the traditional owners of the lands from the remote data collection site.

### Dissemination of findings

All study data will be archived on a secure server at Griffith University for at least 5 years after the last publication. Re-identifiable participant data will be collected on a secure web-based platform (REDCap) and exported to Griffith University servers for archiving. A summary report will be disseminated to participating site practitioners and partner organisations. The community advisory group will support dissemination of outcomes within local communities. Outcomes of the project will be disseminated widely at national and international conferences, published in peer-reviewed journals and disseminated on social media.
